# Coping with Unusual ExperienceS for 12–18 year olds (CUES+): a transdiagnostic randomised controlled trial of the effectiveness of cognitive therapy in reducing distress associated with unusual experiences in adolescent mental health services: study protocol for a randomised controlled trial

**DOI:** 10.1186/s13063-017-2326-4

**Published:** 2017-12-04

**Keywords:** Child, psychotic-like experience (PLE), Community mental health, Cognitive behavioural therapy (CBT)

## Abstract

**Background:**

Childhood ‘unusual experiences’ (such as hearing voices that others cannot, or suspicions of being followed) are common, but can become more distressing during adolescence, especially for young people in contact with Child and Adolescent Mental Health Services (CAMHS). Unusual experiences that are distressing or have adverse life impact (UEDs) are associated with a range of current and future emotional, behavioural and mental health difficulties. Recommendations for psychological intervention are based on evidence from adult studies, with some support from small, pilot, child-specific evaluations. Research is needed to ensure that the recommendations suit children as well as adults. The CUES+ study (Coping with Unusual ExperienceS for 12–18 year olds) aims to find out whether cognitive behaviour therapy for UEDs (CBT-UED) is a helpful and cost-effective addition to usual community care for 12–18 year olds presenting to United Kingdom National Health Service Child and Adolescent Mental Health Services in four London boroughs.

**Methods:**

The CUES+ study is a randomised controlled trial comparing CBT-UED plus routine care to routine care alone. CBT-UED comprises up to 16 sessions, including up to 12 individual and up to four family support meetings, each lasting around 45–60 min, delivered weekly. The primary outcome is emotional distress. Secondary outcomes are change in UEDs, risk events (self-harm, attendance at emergency services, other adverse events) and health economic outcomes. Participants will be randomised in a 1:1 ratio after baseline assessment. Randomisation will be stratified by borough and by severity of mental health presentation: ‘severe’ (an identified psychotic or bipolar disorder) or any ‘other’ condition. Outcomes will be assessed by a trained assessor blind to treatment condition at 0, 16 and 24 weeks. Recruitment began in February, 2015 and is ongoing until the end of March, 2017.

**Discussion:**

The CUES+ study will contribute to the currently limited child-specific evidence base for psychological interventions for UEDs occurring in the context of psychosis or any other mental health presentation.

**Trial registration:**

International Standard Randomised Controlled Trials, ID: ISRCTN21802136. Prospectively registered on 12 January 2015. Protocol V3 31 August 2015 with screening amended.

**Electronic supplementary material:**

The online version of this article (doi:10.1186/s13063-017-2326-4) contains supplementary material, which is available to authorized users.

## Background

Psychosis is a disabling and costly mental health condition [1–6] with adverse social and functional outcomes, even following an at-risk presentation [7, 8]. For adults with psychosis, individual and family based cognitive behavioural therapy/interventions (CBTp and FIp, respectively) are recommended by the United Kingdom National Institute for Health and Care Excellence (UK NICE) [5, 6]. On the strength of the adult evidence base, similar recommendations are made for children and young people under the age of 18 years [4, 9]. The guidance extends the offer of treatment to childhood presentations of psychotic-like, or unusual experiences (such as hearing voices that others cannot, or unfounded worries about being followed or deliberately harmed) in the absence of a formal diagnosis of psychosis, or any other condition, when these are accompanied by distress or adverse life impact (UEDs).

Around 15% of young people in the general population experience UEDs, with the rate increasing to around half of young people referred to Child and Adolescent Mental Health Services (CAMHS) with emotional and behavioural problems [10–14]. The occurrence of non-distressing unusual experiences is higher in younger childhood, and frequency generally decreases with age. However, as frequency decreases, the likelihood of associated distress/adverse impact increases [10, 15, 16]. Severity, distress and less effective coping skills predict a persisting trajectory [17]. UEDs have been associated with a range of poor mental health outcomes and intervention is indicated to reduce current distress and disability, with the potential to additionally increase resilience and reduce future mental health risk [12, 13, 18, 19]. However, for younger adolescents (aged under 14 years), recent guidance suggests that the lack of specificity of UEDs as a risk factor for psychosis contraindicates explicitly preventative interventions [20, 21].

Cognitive behavioural models of psychosis assume a continuum of experience, such that the same psychological processes are hypothesised to drive both the persistence and severity of the cognitive, emotional and behavioural difficulties that are characteristic of psychosis, irrespective of whether or not they reach criteria for a diagnosis [22, 23]. Consistent with this, cognitive therapy has been demonstrated to reduce transition to psychosis for young people (usually aged 14 to 35 years) presenting with an at-risk mental state [24]. However, non-transition is still associated with difficulties in health and functioning, and intervening earlier may offset the accumulation of damaging personal, social and economic effects [7, 8, 25].

UK NICE guidance emphasises the need for trials in children, to build a youth-specific evidence base, both for early intervention with UEDs and for working with young people with UEDs in the context of an identified psychotic condition. Emerging evidence suggests that at least some psychological targets of cognitive therapy are common between adult psychosis and childhood UEDs [11, 14, 26–29], supporting the use of similar therapeutic strategies. However, research also suggests that standard protocols are less effective for younger participants [30]; in a recent trial, for younger participants (mean age 16.5 years, range 14 to 30 years), unadapted CBTp performed no better than generic support [31]. We have shown, in pilot and case series work, that adapted, child-specific cognitive behavioural interventions targeting adolescent psychosis or childhood UEDs are feasible, acceptable, safe and potentially helpful [32–34]. This trial will test our child-specific therapy adaptations, which include: shorter duration of sessions and of therapy as needed; greater emphasis on behavioural change; explicit connection with educational, social, familial, and particularly peer, context, and a focus on the developing sense of self and identity. Given the importance of the familial context [35–38], and as the majority of young people are living with an adult carer (usually an extended family member in a parental role), the intervention includes up to four sessions of family work. The role of the family environment in psychosis in adults has been convincingly demonstrated [37]. Early evidence suggests that parents of young people with UEDs, although often unaware of their child’s unusual experiences, are aware of associated emotional and behavioural difficulties [10, 14, 36]. Parents of young people with UEDs experience higher levels of affective disturbance than the general population, and difficulties in their relationship with their child [36]. Associations between parental criticism, social isolation, coping and affective disturbance, are consistent with a cognitive model of caregiving in psychosis [36, 37]. There are suggestions that parental criticism can exacerbate UEDs [38]. Therefore, it is particularly important to offer family support alongside individual interventions for our target population.

### Study aims

We plan to carry out a phase II interventional, randomised controlled trial, to test the clinical and cost-effectiveness of our adapted CBT for childhood UEDs (CBT-UED), as an adjunct to routine care (treatment as usual, TAU), in reducing distress in adolescents (aged 12–18 years) with UEDs in the context of psychosis or any other presentation, in community CAMHS. The CBT-UED intervention plus TAU condition will be compared to TAU alone. Young people allocated to TAU will be offered the CBT-UED intervention after completing the final trial assessment.

The specific research questions to be addressed are:Are clinical outcomes for young people with UEDs improved by the addition of CBT-UED to routine care?Are the effect sizes comparable to those found in the adult academic literature?Is the intervention cost-effective?

## Methods

### Participants and setting

We aim to recruit 120 young people aged between 12 and 18 years, presenting to CAMHS in four London boroughs served by the South London and Maudsley National Health Service Foundation Trust: Southwark, Lambeth, Croydon and Lewisham. The sample will be transdiagnostic, and will include young people with a diagnosed or emergent psychosis, or any other presentation, treated by the clinical team. However, all participants will have unusual experiences in the form of positive psychotic or psychotic-like phenomena, and associated distress/adverse life impact.

Each borough service carries a caseload of around 500 young people, with around 60 new referrals per month per borough and a workforce of around 70 community mental health workers in total. The teams work with young people whose presentation warrants secondary mental health care; the usual criteria are risks of harm to themselves or others. National incidence rates of psychosis may be exceeded in the target services: a team with 40–60 new referrals/month averages three psychosis referrals/month. Population estimates and our recent work indicate that at least an additional 25–50% of referrals will have UEDs, in the absence of a psychosis diagnosis [10–14]. Based on approaching all new referrals, and assuming a consent rate of 50%, we estimated a recruitment rate of six young people/month.

#### Screening protocol

In order to participate in the CUES+ study, young people need to present with unusual experiences with accompanying distress and/or adverse life impact. Following our earlier pilot work with the target services [34], borough teams routinely administer a measure of unusual experiences (the Unusual Experiences Questionnaire, UEQ) [10, 14, 39, 40] with their standard assessment battery. The UEQ has been shown to be a reliable and valid measure of UEs for young people [12]. Respondents rate each of nine UEs on a 3-point Conviction scale: 0 (not true); 1 (somewhat true); 2 (certainly true); endorsed UEs are rated for Frequency over the past 2 weeks: 0 (not at all); 1 (only once); 2 (2–4 times); 3 (5 + times); Distress (‘How much has it upset you?’) and Adverse Impact (‘How much has it made things hard at home or school?’), both rated: 0 (not at all); 1 (only a little); 2 (quite a lot); 3 (a great deal). Item totals (ratings across dimensions of conviction, frequency, distress, impact, range 0–11), are summed to create a UE-severity score, and, by selecting only those items where distress or impact is rated > 0, a UED-severity score (0–99, higher scores indicate greater severity). We have found this screening procedure to be both feasible and acceptable to young people and their families [34]. Screening is important as UEDs are not otherwise routinely assessed in community CAMHS, and, although parents and other involved agencies may be aware of distress, or behavioural problems, children tend not to report their UEDs unless directly asked [10, 14]. Young people also routinely complete a measure of childhood psychopathology (the Strengths and Difficulties Questionnaire, SDQ) [41, 42]. We initially screened for young people rating any UE > 0 on UEQ conviction, who also had a score in the clinical range (≥7) of the Emotional Problems subscale of the SDQ (SDQ-E) to indicate current distress. However, early recruitment figures (after 6 months of recruitment) showed that 80% of young people endorsing unusual experiences but not meeting the SDQ-E distress criterion were reporting distress and/or adverse impact associated with the unusual experience, and expressing interest in participating in the study. With the agreement of our funders, the clinical service, our Independent Trial Steering Committee and our Research Ethics Committee (REC), we therefore amended the criteria to also include endorsing a UE, with self-rated distress or adverse impact ≥ 0, with no requirement to meet the clinical criterion of the SDQ-E. This was agreed sufficiently close in time to the trial start (December, 2015) for young people who had been excluded at the screening stage to be recontacted regarding participation.

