
#### Inclusion and exclusion criteria

Inclusion criteria are: presenting to local CAMHS; current unusual experience with associated distress and/or adverse impact; aged 12–18 years; intending to be available for the next 6 months in order to complete participation in the study; sufficient English language ability for young people, and parents as relevant, to be able to give informed consent (or assent with parental consent), complete assessment measures and participate in therapy, with interpreter support as appropriate. Exclusion criteria are: having a known learning disability (Intelligence Quotient, IQ < 70, confirmed by the treating team); a UED occurring only secondary to a known neurological condition (e.g. epilepsy or brain injury); limited to states of acute intoxication/withdrawal in the context of substance misuse.

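### As printed, neither screening route requires that the unusual experience itself causes distress or impact, so the screen does not secure the population the protocol describes

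*Protocol article*

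**What the plan says.** All references are to the protocol article.

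**Screening protocol, first route.** "We initially screened for young people rating any UE > 0 on UEQ conviction, who also had a score in the clinical range (≥7"; the sentence continues "of the Emotional Problems subscale of the SDQ (SDQ-E) to indicate current distress".

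**Screening protocol, added route.** After about six months of recruitment, "we therefore amended the criteria to also include endorsing a UE, with self-rated distress or adverse impact ≥ 0", and the SDQ-E cut-off does not apply on this route. The amendment adds to the first route and does not replace it.

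**Screening protocol, scoring.** Distress and adverse impact of each endorsed UE are "both rated: 0 (not at all); 1 (only a little); 2 (quite a lot); 3 (a great deal"). The trial's own UED score is formed "by selecting only those items where distress or impact is rated > 0, a UED-severity score".

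**Target population.** Participants and setting states that "all participants will have unusual experiences in the form of positive psychotic or psychotic-like phenomena, and associated distress/adverse life impact". Inclusion and exclusion criteria asks for "current unusual experience with associated distress and/or adverse impact", with no instrument or cut-off.

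**Recruitment.** Teams invite young people whom the screening measure identifies as having UEDs. Information, consent, baseline assessment and randomisation follow. No further check of UED status is described.

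**Definition.** The Abstract treats a UED as an experience that is itself distressing or has adverse impact. The Background and the opening of Screening protocol ask only that distress or impact accompanies the experience.

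**The concern.** The SDQ-E measures emotional problems in general. A score of 7 or more does not show that the UE is what upsets the young person or disrupts home or school. The UEQ asks exactly that, item by item, but the first route does not use those answers. The added route does refer to them, but at a threshold that the lowest possible rating already meets.

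Two things are at stake. First, the research question concerns young people with UEDs, and the screen can pass people who have none by the trial's own scoring. Second, UED severity at 16 weeks is a secondary outcome. Anyone starting at 0 is at the floor of the 0–99 scale and cannot improve on it. On the primary outcome, SDQ-E at 16 weeks, any benefit in such a person would be a change in general emotional symptoms and would say little about UED-related distress.

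**Working it through.** **1. The scale.** Per UEQ item: conviction 0–2, frequency 0–3, distress 0–3, impact 0–3. The maximum is 2 + 3 + 3 + 3 = 11 per item, and 9 × 11 = 99 over nine items. Both agree with the stated ranges of 0–11 and 0–99.

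**2. A young person with no UED by this scoring.** If distress = impact = 0 on every endorsed item, no item qualifies and UED-severity is 0. Each such item still adds conviction (1–2) plus frequency (0–3), so 1 to 5 points, to UE-severity. A person could therefore score up to 9 × 5 = 45 on UE-severity and 0 on UED-severity.

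**3. Which rating patterns pass.** For one endorsed item there are 2 conviction values, 4 frequency values and 4 × 4 = 16 distress–impact pairs, of which 15 have at least one rating above 0. SDQ-E is either at or above the cut-off or below it. These are counts of possible answers, not of patients.

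| Screening rule | Patterns that pass | Of these, distress = impact = 0 |
|---|---|---|
| SDQ-E route alone | 2 × 4 × 16 × 1 = 128 | 2 × 4 × 1 = 8 |
| SDQ-E route or added route as printed (at least 0) | 2 × 4 × 16 × 2 = 256 | 2 × 4 × 2 = 16 |
| SDQ-E route or added route read as above 0 | 240 + 8 = 248 | 8 |
| Above 0 required on both routes | 2 × 4 × 15 × 2 = 240 | 0 |

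As printed, the added route passes every endorsed pattern and so contains the SDQ-E route. If its threshold is a slip for above 0, the gap narrows from 16 patterns to 8, all through the SDQ-E route. Correcting that sign alone is not enough.

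**4. What happens after the screen.** The inclusion criterion requires associated distress or impact, so the person in step 2 is ineligible on its wording. But that criterion has no measure attached, and Recruitment leaves identification of UEDs to the screening measure. The only operational rule in the article is therefore the one that lets this person through.

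**5. Whether the number can be estimated.** The one relevant figure is that 80% of UE endorsers below the SDQ-E cut-off reported associated distress or impact. It says nothing about those at or above the cut-off, which is the group on the first route. It is also joined to interest in taking part, so the other 20% need not be free of distress. The article does not say how many participants entered by each route. No share, and hence no dilution, can be calculated.

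**The case against.** **The inclusion criterion stands apart from the screen.** Passing the screen leads only to an invitation, and a person without associated distress or impact is formally ineligible. The article is also condensed, so the full protocol may describe a further check, and Figure 1 is not shown. This stands as far as it goes: a reader might infer that young people without UEDs have entered the trial, and the documents do not show that. They show only that such people can pass the screen. What remains is a contradiction within the article, because it names the screening measure as the means of identifying UEDs and the printed rules do not match the stated population.

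**The at-least-0 threshold is probably a slip.** This is plausible, since the reason given for the amendment is that young people were reporting UE-related distress or impact. It does not help the SDQ-E route.

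**General distress may have been intended to count.** The looser definition would allow this, and the primary outcome is itself SDQ-E. That is a fair reading of the Background, but it conflicts with the Abstract and with the UED item rule. The definition needs settling either way.

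**Attribution is a wider matter.** One might say that a positive SDQ-E result could not be credited to UEDs because of this screen. That goes too far. The difficulty comes mainly from using a general emotional score as primary outcome in a transdiagnostic sample, and it would remain after the screen is corrected.

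**Little recruitment is left.** With 111 of 120 randomised, a new rule affects at most 120 − 111 = 9 people. This is true, and it shifts the value of the fix towards reporting and analysis.

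**Conclusion.** The point holds as an inconsistency in eligibility. The retained SDQ-E route does not test UE-related distress or impact, the added route as printed excludes no endorser, and no measure is named for the formal criterion. Young people with a UED-severity of 0 can therefore pass a screen meant to select UEDs. This should be corrected, but it does not invalidate the randomised comparison.

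Its size in patients is unknown. A reader might take the 80% figure to mean that 20% of SDQ-E-route participants have no UED, and scale the 0.6 SD effect in the sample size section down by that share. The documents do not support this. The figure concerns the group below the cut-off, a share of one route is not a share of the trial, and the 0.6 SD comes from earlier cognitive therapy studies and is not tied to UED severity.

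The conclusion rests on reading the amendment as adding a route to the first one, and on the UED-severity item rule being the trial's working definition of a UED.

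**What to change.** Reconcile Participants and setting, Screening protocol, Inclusion and exclusion criteria, and Recruitment so that one rule applies on either route: at least one endorsed UEQ item with distress or adverse impact rated above 0. This matches the UED-severity item rule. Correct the at-least-0 threshold, name the UEQ in the inclusion criterion, and use one definition of a UED in the Abstract, the Background and Screening protocol. Check the rule on the baseline UEQ before randomising any remaining participants.

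For those already randomised, report by arm the number with baseline UED-severity of 0. Add a sensitivity analysis of SDQ-E and UED severity that excludes them. The exclusion uses only pre-randomisation data, so the comparison stays randomised. The full intention-to-treat analysis remains primary.

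The cost is a wording change, one extra baseline row and one extra analysis, all from data already collected. The downside is that a few referrals become ineligible.

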
#### Inclusion and exclusion criteria

Inclusion criteria are: presenting to local CAMHS; current unusual experience with associated distress and/or adverse impact; aged 12–18 years; intending to be available for the next 6 months in order to complete participation in the study; sufficient English language ability for young people, and parents as relevant, to be able to give informed consent (or assent with parental consent), complete assessment measures and participate in therapy, with interpreter support as appropriate. Exclusion criteria are: having a known learning disability (Intelligence Quotient, IQ < 70, confirmed by the treating team); a UED occurring only secondary to a known neurological condition (e.g. epilepsy or brain injury); limited to states of acute intoxication/withdrawal in the context of substance misuse.

### Study design

CUES+ is a parallel-group RCT with random allocation to one of two arms, comparing our active intervention (CBT-UED + TAU) to routine care alone (TAU). Treatment as usual (TAU) will be delivered without interference in both conditions and includes care coordination, practical and emotional support for the young person and their family, and medication as appropriate. We will record what is delivered as routine care. Assessments will take place at baseline (0 weeks), 16 weeks (post therapy) and 24 weeks (2 months post therapy). After 24 weeks, TAU participants will be offered the intervention. Trained research workers will complete assessments with parents and young people. Baseline assessments will be carried out prior to randomisation; 16- and 24-week assessments will be arranged by the trial research worker, but carried out by a different assessor who will be blind to treatment allocation. Service and economic measures will be completed for the 6-month periods before and after baseline. The study design is illustrated in Figs. 1 and 2 (Fig. 2 shows a modified version of the Standard Protocol Items: Recommendations for Interventional Trials (SPIRIT) Figure for the trial).

